**Figure 1 F1:**
[figure not shown]
**CONSORT diagram for the randomized controlled trial of the ****
*Nothing Ventured Nothing Gained intervention.*
**

### *NVNG* online parent and adolescent intervention

*NVNG* incorporates two separate but parallel components: an adolescent intervention and a parent intervention. The intervention is designed for parents and adolescents to complete in parallel and is fully self-directed. Adolescents and parents will be provided with individual login details and will work through most sessions separately. However, some activities will be completed collaboratively (e.g., problem solving strategies). Participants will receive weekly email or text message reminders to log in to complete the sessions.

### Adolescent intervention

The adolescent intervention consists of five sessions completed over a six week period. The intervention is based on cognitive behavioral principles and incorporates a mixture of psycho-education and active learning exercises. The goal of the adolescent intervention is to increase their knowledge of the interface between their illness and adolescent development, to increase self-efficacy and coping, to provide strategies to improve mental and physical well-being, and to build and maintain positive relationships with family and friends.

### Parent intervention

The parent intervention consists of six sessions, intended to be completed over a six week period. The *NVNG* parent intervention aims to provide parents with information and skills to enable them to understand the interface between their children’s illness and normal adolescent development and to develop and maintain trusting, positive and accepting relationships with their adolescent thereby facilitating their transition to independent self-care within safe boundaries.

The intervention is based on the ABCD parenting young adolescents program [30], a group-based parenting program that combines a behavioral family intervention approach with acceptance-based strategies. ABCD targets adolescent behavior, parental well-being, and positive parenting practices. The program incorporates strategies designed to assist parents to maintain a close relationship with their adolescent as they move towards greater autonomy whilst still maintaining clear boundaries. Details of the adolescent and parent intervention content is shown in Table 1.

**Table 1 T1:** Nothing ventured nothing gained Intervention overview

**Session theme**	**Content**
*Adolescent intervention*	
Session 1: Adolescent development and diabetes management	● Adolescence: physical, cognitive and social changes during adolescence.
	● Challenges of managing T1D during adolescence.
	● Links to T1D management resources.
Session 2: Connection between thoughts, feelings and behavior	● Understanding the relationship between thoughts, feelings and behaviors.
	● Recognizing signs of stress, anxiety and depression.
	● Recognizing and challenging unhelpful thoughts.
	● Accessing support.
Session 3: Communication	● Communicating with parents and handling difficult conversations.
	● Importance of body language, assertiveness, and confidence.
	● Communicating when feeling angry and frustrated.
Session 4: Building strong relationships	● Identifying values relating to relationships.
	● Relationships with parents and friends.
	● Steps to effective problem solving.
	● The effects of and managing bullying.
Session 5: Staying healthy	● Finding the balance between diet, exercise, work, sleep and leisure time.
	● Barriers to a healthy balance: peer pressure, smoking, alcohol, and other drugs.
	● Maintenance: Setting goals and problem solving to maintain the balance.
*Parent intervention*	
Session 1: Raising an adolescent with diabetes	● Adolescence: physical, cognitive and social changes during adolescence.
	● Adolescent cognitive processes and how they impact parent-adolescent interactions.
	● Challenges of managing T1D during adolescence.
	● Links to T1D management resources.
Session 2: Strengthening the parent-adolescent relationship	● Parenting values.
	● Ways of connecting with adolescents.
Session 3: Adolescent independence and safety	● A model for adolescent autonomy granting.
	● How to effectively use praise.
	● Demonstrating acceptance.
Session 4: Communication and problem solving	● Listening and talking to adolescents.
	● Barriers to communication.
	● Problem solving.
Session 5: Setting boundaries	● Limit setting and rules.
	● Characteristics of effective consequences.
Session 6: Parent self-care	● Parent health and well-being.
	● Recognizing and accessing support.
	● Managing stress.

### Measures

Outcomes will be assessed via self-administered adolescent and parent-report questionnaires. Measures were chosen for their sound psychometric properties, and their relevance to the primary and secondary outcomes. Participants may complete assessments online or via a pen and paper version (according to participant preference).

### Glycosylated hemoglobin (HbA1c)

Metabolic outcomes will be measured using glycosylated hemoglobin (HbA1c) which is a measure of glycemic control based on average blood glucose concentration levels in the 3 to 4 month period prior to the HbA1c test [56,57]. HbA1c levels which are collected as part of the adolescents’ routine care at the regular clinic visit will be obtained from the participants’ endocrinologist at four time points over a 12 month period (two levels prior to commencement in the study, and the two levels following completion of the intervention/waiting period).

Parent and adolescent self-report instruments used to collect data from participants, including primary and secondary outcomes, are listed in Table 2.

**Table 2 T2:** Parent and adolescent self-report measurement tools and questions at each time point

		**Time point**		
	**Measurement tools/questions**	**Baseline**	**Post**	**Follow-up**
**Demographics**				
Adolescent characteristics	Age, gender, postcode, family Characteristics, living arrangements, education, age at diagnosis, family history of diabetes, diabetes treatment regime, number of hospitalizations, general medical history (Other Acute or chronic health conditions)	✓		
Parent characteristics	Age, gender, postcode, education, marital status, and employment			
**Process evaluation**				
Satisfaction with intervention**^**	6 item assessment rating the intervention with 4 additional open-ended questions regarding most liked, least liked, suggestions on improvements, and other comments		✓	
**Primary outcome**				
**Adolescent**				
Mental health	Children's depression inventory -short form (CDI -S) [58]	✓	✓	✓
	Revised children's manifest anxiety Scale (RCMAS -S) [59]	✓	✓	✓
**Secondary outcomes**		✓	✓	✓
**Adolescent**				
Behavioral	Self-care inventory (SCI-R) [60]	✓	✓	✓
	Adolescent risk taking questionnaire (ASQ) [61]	✓	✓	✓
Psychosocial	Diabetes quality of life survey for youths (DQoLY-S) [62]	✓	✓	✓
	Child health questionnaire: parent form 50 (CHQ-PF50) [63]	✓	✓	✓
	Stanford diabetes self-efficacy scale (SDSES) [64]	✓	✓	✓
	Benefit burden scale for children (BBSC) [65]	✓	✓	✓
	Adolescent resilience scale (ARS) [66]	✓	✓	✓
Metabolic	HbA1c	✓		✓
**Parent**				
Psychosocial	Depression, anxiety & stress scale (DASS) [67]	✓	✓	✓
	Fatigue assessment scale (FAS) [68]	✓	✓	✓
	Parent sense of competence scale (PSoC) [69]	✓	✓	✓
	Parent experience of child illness (PECI) [70]	✓	✓	✓
**Family**				
Communication	Family problem solving communication index (FPSCI)* [71]	✓	✓	✓
	Family management measure (FaMM) [72]	✓	✓	✓
Reduced conflict	Diabetes family conflict scale (DFCS)* [73]	✓	✓	✓
Diabetes responsibility	Diabetes family responsibility questionnaire (DFRQ)* [74]	✓	✓	✓
**Mediators and moderators**				
Perceived social support	Adolescent satisfaction with support from parents, boyfriend/girlfriend, friends, teachers, employers, diabetes specialists	✓	✓	✓
Other activities	Engagement in employment and extra-curricular activities.	✓		

^Administered to intervention group only.

*Administered to parents and adolescents.

### Process measures

Process variables, assessed at post-test include intervention dosage (% of modules accessed as recorded on the web interface), parent and adolescent perceptions of strengths and weaknesses of the intervention including appropriateness of the content, usability, satisfaction and acceptability of the web interface, and reason for non-participation/non-completion of the intervention (where relevant).

### Data analysis

Similarity of baseline characteristics of intervention and control participants will be assessed using appropriate summary statistics. Multi-level modeling will be used to compare the outcomes of participation in the intervention and wait-list control arms of the study in terms of pre-/post changes in primary and secondary outcomes while controlling for geographic region, age, gender, and other relevant confounds. Any imbalances in baseline characteristics between the study arms will also be controlled for in the model. Baseline data will be investigated to see if there are any significant factors associated with those participants who drop out in comparison to those that do not, to check for bias. By doing so we will be able to analyze the final results for attrition bias using the predicted probability of attrition as recommended by Heckman [75] and Rubin [76]. An intention to treat analysis and then a longitudinal hierarchical linear model analysis will be conducted, avoiding the need to impute missing data.

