## Methods/Design

The study will evaluate the efficacy, acceptability, and usability of the *NVNG* intervention with approximately 120 adolescents with T1D and their parents in Victoria, Australia. An RCT design, using repeated measures with two arms (intervention and wait-list control), will be used to assess the efficacy of the *NVNG* intervention. Outcomes for participants in both study arms will be assessed at three time points, at baseline (Time = 0), post-intervention/wait (Time = 6 weeks) and follow-up (Time = 6 months).

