### Sample size calculation

Given that there are no meta-analyses available for internet interventions of family centered parenting and adolescent programs, studies reporting face-to-face parenting and adolescent interventions and internet interventions directed at health behavior change were used to inform power calculations [50]. A meta-analysis of psychological interventions to improve outcomes in children and adolescents with T1D reported a moderate effect of family therapy on child/adolescent psychological distress (ES = .46) and HbA1c (ES = .41) [51]. A meta-analysis of internet interventions aiming to promote adolescent health related behaviors showed moderate effects (ES = .33) for interventions grounded in Cognitive Behavioral Theory or Theory of Planned Behavior [44]. Therefore a medium effect size is expected on the primary adolescent mental health outcome measure, as measured by the CDI and the RCMAS-S, between the two groups across the three assessment points. To power the study at the 80% level, based on an alpha level of .05, with an estimated medium effect size (.40) and with two groups over three assessment points, 64 complete responses will be required. Given that self-help online intervention studies often report high attrition rates (e.g. [52,53]), we have allowed for a 30% attrition rate between baseline and pre-assessment, and a further 20% attrition rate between post and follow-up; therefore a total of approximately 120 participants will be required; 60 per group.

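### The arms are compared on pre-/post change, with the outcome's own baseline score not named as a covariate and further baseline adjustment dependent on observed imbalance, which gives up precision

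*Protocol article*

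**What the plan says.** The Data analysis section of the protocol article plans multi-level modelling to compare the two arms "in terms of pre-/post changes in primary and secondary outcomes while controlling for geographic region, age, gender, and other relevant confounds". The next sentence adds: "Any imbalances in baseline characteristics between the study arms will also be controlled for in the model". The section closes with: "An intention to treat analysis and then a longitudinal hierarchical linear model analysis will be conducted, avoiding the need to impute missing data".

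Methods/Design sets the assessments "at baseline (Time = 0), post-intervention/wait (Time = 6 weeks) and follow-up (Time = 6 months". The primary hypothesis concerns both later times. According to Table 2, both primary scales (CDI-S and RCMAS-S) and all secondary questionnaires are scored at baseline as well as later. The Randomization procedure section places randomization after the baseline questionnaire.

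Nowhere does the article say whether the baseline score enters the model as a response or as a covariate, or whether the arms share a baseline mean. It gives no within-person correlation.

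**The concern.** Because randomization follows the baseline questionnaire, the two arms have the same expected baseline score. A model that uses this fact estimates the same treatment effect as a comparison of changes and, in large samples, never with greater variance. A model that does not use it carries the noise of the baseline difference into the estimate.

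The rule for further adjustment also rests on the wrong trigger. The benefit of adjusting for baseline depression or anxiety comes from its correlation with the later score, not from whether the arms happen to differ. If adjustment depends on observed imbalance, the gain is lost whenever the arms look alike, and the form of the primary model stays open until the data have been seen.

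What is at stake is the width of the confidence interval for every outcome scored at baseline, in a trial that expects to keep little more than half of its participants to 6 months.

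**Working it through.** **Inputs from the article (Sample size calculation).** Power: "To power the study at the 80% level". Other inputs: "based on an alpha level of .05, with an estimated medium effect size (.40) and with two groups over three assessment points, 64 complete responses". Attrition: "we have allowed for a 30% attrition rate between baseline and pre-assessment, and a further 20% attrition rate between post and follow-up". Total: "a total of approximately 120 participants will be required; 60 per group". I read the first attrition step as loss by the 6-week assessment, although the text calls it pre-assessment.

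**Inputs assumed.** r is the correlation between baseline and later score, given the other covariates; .3 to .8 is examined because the article has no figure. Variances are equal at all times, with the same r between any two. For power only: .40 is a standardised mean difference and the test is two-sided at .05.

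**The plan's own figures.**
- Retention: 0.7 × 0.8 = 0.56. Then 120 × 0.56 = 67 completers, and 64/0.56 = 114.3, so 115. Both are close to the planned 120.
- The 64 completers cannot be reproduced from the stated inputs. A two-sample t-test at a standardised difference of .40 needs 100 per arm. A group-by-time test over three assessments comes near 64 only at an unstated r of about .2 (66 in total). This is a separate question about sample size.

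**Complete data, one later time point.** In units of the outcome variance, per participant:
- change score: 1 + 1 - 2r = 2(1-r)
- baseline-adjusted: 1 - r²
- difference: 2(1-r) - (1-r²) = (1-r)², never negative
- share of information lost: (1-r)² / [2(1-r)] = (1-r)/2

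| r | change | adjusted | lost |
|---|---|---|---|
| .3 | 1.40 | 0.91 | 35% |
| .5 | 1.00 | 0.75 | 25% |
| .6 | 0.80 | 0.64 | 20% |
| .7 | 0.60 | 0.51 | 15% |
| .8 | 0.40 | 0.36 | 10% |

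Below r = .5 the change score has variance above 1, so it does worse than ignoring the baseline. A multi-level model with free baseline means in each arm, complete data and an arm-by-time contrast loses the same shares. Calling the model multi-level does not by itself remove the loss.

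**Longitudinal model with the planned attrition.** Compare free baseline means with a common baseline mean, n per arm, 70% observed at 6 weeks and 56% at 6 months. Variances are per arm, times n.

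*6 weeks.* Common mean: A = (1-r²)/0.7. Free means: A + (1-r)².
- r = .5: A = 0.75/0.7 = 1.071; lost 0.25/(1.071 + 0.25) = 19%
- r = .7: A = 0.51/0.7 = 0.729; lost 0.09/(0.729 + 0.09) = 11%

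*6 months.* Common mean: B = v/0.56 + b²(1-r²)/0.7, with v = (1-r)(1+2r)/(1+r) and b = r/(1+r). Free means: B + (1-r)².
- r = .5: v = 0.667, b = 0.333, B = 1.190 + 0.119 = 1.310; lost 0.25/1.560 = 16%
- r = .7: v = 0.424, b = 0.412, B = 0.756 + 0.124 = 0.880; lost 0.09/0.970 = 9%

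A numerical comparison of the two models' information matrices gives the same figures.

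**What it means for power, if .40 is a standardised mean difference.** With 67 completers and one time point, power goes from 36% (change) to 46% (adjusted) at r = .5, from 44% to 52% at r = .6, and from 55% to 62% at r = .7. Completers needed for 80% power are 200 against 150, 160 against 128, and 120 against 104.

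**The case against.** The strongest reply is that the article does not exclude the baseline score. Its covariate list is open-ended, the imbalance clause could take in an imbalanced baseline CDI-S or RCMAS-S score, and a longitudinal model with a common baseline mean fits the wording. Comparing arms on change need not mean that change is the dependent variable; even if it is, adding baseline as a covariate gives the same treatment estimate as modelling the later score with that covariate. The article is condensed, and model parametrisation is commonly left to an analysis plan.

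Much of this stands. A reader might infer that the baseline score is ruled out, but the text leaves it unnamed, no more. A reader might also take 15% to 25% as the loss in this trial; that range holds only for an assumed r of .7 to .5, a complete-data contrast and no recovery through the imbalance clause or a common baseline mean.

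What does not stand is that this is only missing detail. The article states the contrast, names three covariates and states a rule for adding more. That rule turns on observed imbalance, which is the wrong criterion for a prognostic variable in a randomized comparison. In a randomized trial the baseline score is not a confounder, so the phrase about other relevant confounds does not reliably bring it in.

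**Conclusion.** The point holds as one about precision. The stated contrast, the named covariates and the imbalance-triggered rule together do not ensure that the baseline score is used. If it is not used, the loss is (1-r)/2 with complete data: 35% to 10% for an assumed r of .3 to .8. Under the planned attrition in a longitudinal model it is about 19% to 11% at 6 weeks and 16% to 9% at 6 months for r = .5 to .7. These figures rest on equal variances, a constant correlation and an r that the article does not supply.

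Two stronger readings are not supported. First, a difference in change is not systematically biased here: under randomization it estimates the same effect, less precisely. Second, a reader might conclude that the trial is short of power and that baseline adjustment would repair it. The article does not say what kind of effect size .40 is, so the shortfall depends on reading it as a standardised mean difference. On that reading, adjustment still needs 150 to 104 completers at r = .5 to .7, against 64 planned. The sample-size question has to be settled separately.

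**What to change.** In Data analysis, state the primary model as a mixed model for the 6-week and 6-month scores, with arm, time as categories, arm-by-time, region, age and gender. State that the baseline score of the same scale is always included as a covariate (or that the arms share a common baseline mean), whatever imbalance is observed. Drop observed imbalance as the trigger for adjusting for the baseline score. Use the same form for every secondary scale measured at baseline.

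The cost is wording only: no new data, visits or participants. Trial status reports that data collection is still under way, so the model can be fixed before the outcomes are analysed.

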### Primary outcomes

Primary outcomes will be adolescent mental health (depression and anxiety). Our primary hypothesis is that adolescents randomized to receive the *NVNG* intervention immediately, will demonstrate significantly better mental health (lower levels of depression and anxiety) than adolescents in the wait-list control group, from pre- to post-intervention and at the 6 month follow-up.

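### The covariate-adjusted arm comparison is tied to change up to 6 weeks, while the primary hypothesis also claims a 6-month benefit; the longitudinal model listed after it is not tied to that hypothesis or to the covariates

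*Protocol article*

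**What the plan says.** All references are to the protocol article.

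- **Primary outcomes.** Adolescents given the intervention at once are expected to have less depression and anxiety than the wait-list group "from pre- to post-intervention and at the 6 month follow-up". Both time frames belong to the primary hypothesis.
- **Methods/Design (opening paragraph) and Table 2.** There are three assessments: baseline, post at 6 weeks and follow-up at 6 months. The two primary scales, the CDI-S and the RCMAS-S, are collected at all three.
- **Sample size calculation.** The effect is expected "between the two groups across the three assessment points", and the requirement is stated "with an estimated medium effect size (.40) and with two groups over three assessment points, 64 complete responses will be required".
- **Data analysis.** Multi-level modelling compares the arms "in terms of pre-/post changes in primary and secondary outcomes while controlling for geographic region, age, gender", together with other confounders and any baseline imbalances. After a passage on attrition, the section closes: "An intention to treat analysis and then a longitudinal hierarchical linear model analysis will be conducted", which is said to make imputation unnecessary.

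**The concern.** The one arm comparison described with its covariates stops at 6 weeks if the protocol's own terms are applied. It therefore does not test the 6-month half of the primary hypothesis and does not match the three-assessment basis of the sample size.

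The closing sentence could supply what is missing, but it does not say that the longitudinal model is the test of the hypothesis, which arm differences it estimates, or whether the named covariates carry over. It also sets intention to treat beside a model as though the two were successive analyses. Intention to treat says who is analysed and in which arm; it is a property of the mixed model, not a step before it.

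Two things are at stake. The text leaves open which result decides the primary hypothesis on each scale. And a comparison of change from baseline is less precise at 6 weeks than one adjusted for the baseline score.

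**Working it through.** **1. Does the post assessment mean 6 weeks throughout?** The opening of Methods/Design defines it so and names the 6-month visit separately. The primary hypothesis, the attrition allowance, the reminders described under Study arms, the columns of Table 2 and Trial status all keep post and follow-up apart. The plain reading of the covariate-adjusted comparison is therefore baseline to 6 weeks.

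**2. The plan's own sample size.** Inputs: "To power the study at the 80% level, based on an alpha level of .05", effect .40, two groups, three assessments. A fixed-effects analysis of variance for the group-by-time interaction, with .40 read as Cohen's f, numerator df 2, 6 cells and noncentrality N × f², gives:
- N = 63: power .797
- N = 64: noncentrality 64 × .16 = 10.24, denominator df 58, power .804

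So 64 is reproduced by a calculation that uses three time points (a one-way comparison of three groups with f = .40 also gives 64). Attrition of 30% and then 20% gives 64 / (.7 × .8) = 114.3, or 115, against the approximately 120 stated; 120 × .56 = 67 completers.

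**3. Precision of the 6-week contrast.** Taken from the plan: 60 per arm and 30% first-stage attrition, so 60 × .7 = 42 per arm. The protocol words that stage as "we have allowed for a 30% attrition rate between baseline and pre-assessment"; I take it as loss before the 6-week visit. Assumed: standardised mean difference d = .40, SD 1, two-sided .05, normal approximation, correlation r between baseline and 6 weeks of .3, .5 or .7.

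- Change score: SE = √(2 × 2(1 − r)/42)
- Baseline-adjusted: SE = √(2(1 − r²)/42)
- Power = Φ(.40/SE − 1.96)

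| r | SE, change | Power, change | SE, adjusted | Power, adjusted |
|---|---|---|---|---|
| .3 | .258 | .34 | .208 | .49 |
| .5 | .218 | .45 | .189 | .56 |
| .7 | .169 | .66 | .156 | .73 |

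The ratio of variances is 2(1 − r)/(1 − r²) = 2/(1 + r), that is 1.54, 1.33 and 1.18. This ratio does not depend on the effect size.

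**4. What the third visit adds.** Under the same assumptions, with 42 × .8 = 33.6 per arm at 6 months and equal correlation between all visits, a baseline-adjusted longitudinal model gives the same power for the 6-week contrast (.49, .56, .73) and .41, .48 and .65 for the 6-month contrast. The extra visit gives no power at 6 weeks. It gives an estimate of the 6-month effect, which the hypothesis requires.

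**5. Sensitivity to the effect metric.** If .40 is Cohen's f, then d = .80 for two groups. At r = .5 the powers become Φ(.80/.218 − 1.96) ≈ .96 and Φ(.80/.189 − 1.96) ≈ .99, so the gap almost closes. In the calculation that reproduces 64, dropping to two time points (numerator df 1, 4 cells, N = 64) raises power from .80 to .88.

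**The case against.** The strongest reply is that multi-level model and hierarchical linear model name the same class of method, so the section may describe one longitudinal model twice, with the pre/post wording a loose phrase for change from baseline. An article also condenses, and the choice of primary model and covariates is often left to the analysis plan.

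Part of this stands. A reader might infer that the 6-month data are discarded; the closing sentence of the section rules that out. A reader might also count three rival tests per scale and infer selective reporting; the text allows that count but does not establish it.

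A reader might further infer that power is lost outright. The document does not support this: it gives no correlation, does not say whether .40 is d or f, and the calculation that returns 64 has more power with two time points than with three. Nor does a multi-level model have to be a raw change score. It does, however, give the change-score comparison with two visits, complete data and arm means left free at baseline, and nothing in the section says that the baseline score is adjusted for.

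What the reply does not meet is the stated time frame. The protocol separates post from follow-up consistently, so the sentence as written conflicts with the hypothesis. That is a mismatch in what is stated, not a detail left for later, and an analysis plan that follows the text would inherit it.

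**Conclusion.** The point holds as a mismatch that should be corrected; it is not a fatal flaw. The covariate-adjusted comparison as worded does not test the 6-month half of the primary hypothesis. The model that could test it is present, but is not tied to the hypothesis or the covariates. Intention to treat is misplaced as a separate analysis. None of this depends on any power figure.

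The efficiency argument is secondary and conditional. At 6 weeks, a change comparison has 1.18 to 1.54 times the variance of a baseline-adjusted one for correlations of .7 down to .3. At d = .40 that is a difference of roughly .07 to .14 in power; if .40 is Cohen's f, it is small.

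**What to change.** Replace the pre/post sentence and the closing sentence of Data analysis with one primary analysis for each primary scale (CDI-S and RCMAS-S):

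- A mixed model on all randomised adolescents in their assigned arm, using all available assessments. State that this is the intention-to-treat analysis.
- Adjustment for region, age, gender and the baseline score. Baseline enters either as a covariate for the two later visits, or as an outcome with the arm means constrained equal at baseline, but not both.
- Arm-by-visit terms, with the 6-week and 6-month arm differences estimated as the contrasts that the primary hypothesis claims.
- Any model restricted to baseline and 6 weeks labelled a sensitivity analysis.

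A contrast averaged over the two later visits is not required: the hypothesis does not state one, and an average can be significant without a 6-month effect.

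The cost is slight rewording and analysis work. Trial status reports that data collection is still under way, so the change can be made before the data are final, with no new data and no more participants.

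### Beyond region, age and gender, the covariates of the primary model are to be picked by observed baseline imbalance and an open clause, so the set is not fixed in advance

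*Protocol article*

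**What the plan says.** The Data analysis section plans multi-level modelling to compare the arms "in terms of pre-/post changes in primary and secondary outcomes", "while controlling for geographic region, age, gender, and other relevant confounds". The next sentence reads "Any imbalances in baseline characteristics between the study arms will also be controlled for in the model". Imbalance is judged as follows: "Similarity of baseline characteristics of intervention and control participants will be assessed using appropriate summary statistics". The section gives no threshold for imbalance and no closed list of candidate variables. It names no unadjusted or fixed-covariate analysis as primary, and it does not confine imbalance adjustment to a sensitivity analysis.

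The rule applies to the primary outcomes, adolescent depression and anxiety. Under Randomization procedure, allocation is by a computer algorithm after the baseline questionnaire is completed. Under Trial status, data collection is still in progress.

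**The concern.** Differences between randomized arms at baseline are chance. Adjusting for a covariate helps when it predicts the outcome, whether or not it happens to differ between arms. A rule triggered by imbalance selects on the wrong property: it can bring in variables unrelated to depression or anxiety and leave out predictive ones that happen to be balanced. The final model then differs from one possible allocation to the next, and the p-value does not belong to a model that could have been written down beforehand.

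The vagueness adds to this. What counts as an imbalance is not defined, and "and other relevant confounds" has no list. Both decisions could be made after the outcomes are known. The planned number of complete responses is small, so the choice of covariates could move a borderline result across .05.

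**Working it through.** The plan gives no figure for this point. The check is how open the covariate set is, and what the rule does to error rate and power.

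**1. Which covariates are fixed.** Region, age and gender are named. Everything else enters through the open clause or the imbalance sentence.

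**2. How large the candidate pool is.** Table 2 lists 11 adolescent characteristics, among them "living arrangements, education, age at diagnosis, family history of diabetes, diabetes treatment regime, number of hospitalizations, general medical history", and 6 parent characteristics: 11 + 6 = 17. Taking out adolescent age, gender and postcode (if postcode stands for region) leaves 17 − 3 = 14, before counting the baseline questionnaire scales.

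**3. How often the set would vary by chance.** This needs a criterion that the article does not give. As an illustration only, assume K independent variables and a difference at p < .05 as the trigger. The chance of at least one imbalance is 1 − .95^K:

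- K = 5: 23%
- K = 10: 40%
- K = 20: 64%

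The baseline scales are probably correlated and no 5% test is stated, so none of these is an estimate for this trial. They show only that the set would often depend on chance.

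**4. Size of the test under the written rule.** The sample size section gives "based on an alpha level of .05, with an estimated medium effect size (.40) and with two groups over three assessment points, 64 complete responses". This is a total: with the stated attrition, 120 × 0.7 × 0.8 = 67.2. So 64 completes means 32 per arm.

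*Covariates only, baseline score not modelled* (n = 64 or 120; 5 or 10 covariates explaining 30% or 50% of outcome variance, all assumed; 6000 null trials per setting):

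| Strategy | Type I error |
|---|---|
| No covariates | 4.6 to 5.3% |
| Add covariates imbalanced at p < .05 | 3.5 to 4.3% |
| Always add all covariates | 4.5 to 5.3% |

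Monte Carlo error near 5% is √(.05 × .95 / 6000) = 0.28 percentage points, so 3.5% is clearly below nominal and 4.3% is (5 − 4.3)/0.28 = 2.5 standard errors below.

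*Baseline score already in the model*, closer to what is planned (32 per arm, baseline-outcome correlation .6, other coefficients .2, all assumed): the imbalance rule gave 3.5 to 4.8%, against about 5% for a fixed set.

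The direction is as expected. An unadjusted false positive often comes from a chance imbalance in a prognostic variable. Adjusting in just those trials removes some false positives, while the remaining trials keep the wider unadjusted standard error.

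**5. Power.** With 33 per arm, d = .40, baseline always in the model (correlation .6) and one further covariate (coefficient .2), all assumed:

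- added only if imbalanced at p < .05: 50.1%
- always added: 51.8%

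The difference is 51.8 − 50.1 = 1.7 points, and type I error was 4.7% in both cases. In the 32-per-arm check of step 4, the imbalance rule gained no power over a fixed model with the baseline score alone.

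**The case against.** **The article is condensed and an analysis plan may exist.** Which variables count as relevant confounders, and what counts as imbalance, are details often left to such a plan, and their absence alone would not be a finding. That stands. The imbalance sentence is different: it is a positive statement of what will be done, and a plan with a closed list would have to override it.

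**Adjusting for an observed imbalance protects against a misleading comparison.** This is fair for a prognostic variable. But it argues for adjusting for prognostic variables in every case, which a fixed set does without waiting for an imbalance.

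**Stronger readings that the document does not support.**

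- *A reader might infer that the whole primary model is chosen after seeing the data.* It is not: the model class and three covariates are stated in advance.
- *A reader might infer an inflated type I error.* Rates of 10 to 13% do appear in simulation, but only if several models are fitted and the most favourable is kept. The article describes no such search, and the imbalance rule uses baseline data alone.
- *A reader might infer a large loss of power.* A contrast of 35% against 51% arises if a covariate correlated .6 with the outcome is ignored unless imbalanced. The obvious predictor of that strength is the baseline score. Table 2 has both primary scales measured at all three time points, so the planned longitudinal model already uses it.
- *A reader might quote 54% as the chance of a false imbalance* (15 independent variables tested at 5%). Neither the test, the threshold nor independence is in the text.

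**Conclusion.** The point holds in a limited form. The article commits to a data-dependent rule for part of the covariate set of the primary model, and nothing elsewhere in it closes that set. Followed mechanically, the rule is mildly conservative (about 3.5 to 4.8% at a nominal 5%) and brings no power that a fixed model lacks. It is unhelpful, not inflating. These sizes rest on an assumed p < .05 trigger and on assumed covariate and baseline correlations, since the article gives none.

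The remaining risk cannot be given a number from the document: an undefined criterion and an open confounder clause leave discretion after outcomes are known. The wording should be changed, but the point does not undermine the trial and alters no sample-size figure.

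**What to change.** Delete the imbalance sentence and the open confounder clause from the primary model. Before the final data are analysed, fix the covariates as geographic region, age and gender. Use the baseline score of the outcome once, either as the first response in the longitudinal model or as a covariate for the later scores. Doing both would use the same measurement twice. Report any model that adds imbalanced variables as a labelled sensitivity analysis.

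The cost is analysis wording only, with no change to recruitment, measurement or sample size. The downside is small: a chance imbalance in a variable outside the list is addressed only in the sensitivity analysis.
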